## Methods/design

### Design and participants

Study design is detailed in the appendix (Fig. 1 for design and inclusion/exclusion criteria). We will aim to recruit 150 PWT1D with 50% of men and women, and we will recruit participants, in part, from visible minority populations. Participants will be recruited through endocrinology clinics in Québec City and Montreal, Canada and through the BETTER registry [33]. All assessments (inclusion visit, questionnaires, or tasks) will be completed online through secured platforms.

**Fig. 1 Fig1:**
[figure not shown]
Schematic representation of the methodology for the “Sugar Swing study”. *Legend:* CGMS: continuous glucose monitoring system; CV: coefficient of variation; BMI: Body Mass Index; PHQ-9: Patient Health Questionnaire; GAD-7: General Anxiety Disorder; DNT: Diabetes Numeracy Test; DBRS: Diabetes Behavior Rating Scale; T1-DDS: Type 1 Diabetes Distress Scale; EDE-Q: Eating Disorder Examination Questionnaire MAIA v2: Multidimensional Assessment of Interoceptive Awareness; mYFAS: modified Yale Food Addiction Scale; ADHD: Attention Deficit Hyperactive Disorder; eGDR: estimated Glucose Disposal Rate; *e.g., CGMS < 10 days, missing data > 15%

### Quantitative measures

#### Inclusion visit

During this visit conducted online (e.g., using Zoom® or Teams®), the following data will be collected: socioeconomic data, ethnicity, education level, marital status, self-identified gender, diabetes duration, age of diabetes onset, modality of insulin delivery (pump vs injections; closed loop delivery systems are excluded from the present study) and total daily insulin dose, modality of glucose-monitoring (capillary glucose testing or CGMS), duration of CGMS usage, number of severe hypoglycemic episodes over the last year and diabetic ketoacidosis, current medications (included use of psychotropic drugs to be considered as a potential confounding factor), number and type of chronic diabetes micro and macrovascular complications, and medical comorbidities (including hypertension); measured CV based on previous CGMS (e.g., data uploaded during the visit) and last available HbA1c (max 6 months); weight, height and waist circumference (self-measured by the participant as previously described [33]). During this visit, self-management’s skills will be assessed using the *Diabetes Behavior Rating Scale* and the *Type 1 Distress Scale* (a 28-item self-administered questionnaire [34]). Using short screening tests, anxiety (*GAD-7*, 7 items), depression (*PHQ-9*, 9 items) and diabetes numeracy (*Diabetes Numeracy Test*, 15 items, used as proxy for literacy) will be assessed.

#### Glucose variability and insulin resistance

CGMS will be performed over a 10-day period using a Dexcom G6 and data reported following the international consensus [35, 36]. Required material and assistance will be provided by mail if needed. In the province of Quebec (Canada) both the Freestyle Libre and Dexcom are eligible for reimbursement by the public insurance plan for most PWT1D. For the few patients who would not have access to CGMS yet, we will provide the equipment for the duration of the study and a set of sensors will be sent to all participants, as a courtesy for participating in the study. Glucose Management Indicator (GMI) will be used to estimate A1C from CGMS during the study time. The estimated Glucose Disposal Rate (eGDR) will be computed (eGDR is a validated tool for estimating insulin sensitivity in T1D; eGDR = 21.158 + -0.09 × waist circumference − 3.407 × hypertension [defined as 0 = no, 1 = yes] − 0.551 × HbA1c). During the period of CGMS recording, PWT1D will be invited to track their dietary intakes using image-assisted food tracking mobile application over 2 days at random (one weekday and one weekend day) with the Keenoa® application [37].

#### Eating behavior and cognitive tasks

Self-report questionnaire and cognitive tasks will be distributed over 3 sessions of 30 to 45 min each. The session will be scheduled during the 10-day of CGMS measure. Session order will be randomly determined for each participant and each session will start with a short video describing the objectives and procedures. Each session will cover more than one psychological or cognitive domain in order to get different timepoint assessments for each construct.

Glycemic value before and after each session will be collected from CGMS (if participants are experiencing or have experienced hypoglycemia within the last hour, they will be asked to postpone the session) and participants will be asked to perform each session in the same condition (i.e., time of day, location, computers). ***Session A:*** Eating behavior will be assessed by the *Eating Disorder Examination Questionnaire* (a 36-item questionnaire to measure of the range and the severity of eating disorder feature over the past four weeks [38]) and by the *Binge Eating Scale* (a 16-item questionnaire assessing the severity of binge eating behavior [39]). During this session, cognitive flexibility will be assessed by the *Detail and Flexibility Questionnaire* (a 24-item questionnaire validated in eating disorder and exploring difficulties in flexibility/cognitive rigidity and attention to detail/weak central coherence [40]). Attention will be measured by the *Category Switch Task* (a test of divided attention with two simple categorization tasks [41]) and attention Deficit Hyperactive Disorder will be screened by the *Adult ADHD Self-Report Scale* (6 items) [42]. ***Session B:*** The level of interoception will be assessed by the *Multidimensional Assessment of Interoceptive Awareness version 2* (a 32-item questionnaire to measure the conscious level of interoception’s multiple dimensions [43]). This session will also include 3 neurocognitive tasks: the *Tower of London task* (an assessment of executive functioning with a focus on planning abilities [44]), the *Stop Signal Task* (an assessment of impulsivity through the time needed to inhibit a prepotent response [45]), and the *5-Trial Adjusting Delay Discounting* (a quick procedure to estimate delay discount rates of monetary rewards [46]). ***Session C:*** During this session, we will conduct an *Emotional Go/No-Go Task* (a measure of inhibition leverages by emotion recognition and regulation [47]) and the *Attentional Cueing Procedure* (a conditional learning paradigm to study the effects of threat stimuli on capturing and holding attention). Behavioral impulsivity will be measured by the *Short UPPS-P Impulsive Behavior Scale* (a 20-item self-report questionnaire assessing impulsivity as a multifaceted construct [48]). Susceptibility to food reward will be estimated using the *modified Yale Food Addiction Scale 2.0* (a 13-item questionnaire assessing food addiction [49]).

#### Qualitative measures

To further our understanding of the PWT1D experience and factors impacting glycemic self-management, individual in-depth face-to-face (virtual) interviews will be led by a trained investigator (research coordinator) using a semi-structured, open-ended guide. The semi-structured interview protocol will be designed with the involvement of patients’ partners, psychologists and diabetologists. Questions about facilitators and barriers associated with glycemic management, with particular attention to those associated with cognitive function and eating behaviors, will be asked. Participants will also be questioned about the type of therapeutic approaches they need to help them cope with T1D. Interviews will be recorded, transcribed verbatim, and coded. Inductive thematic content analysis will be conducted independently by 2 members of our team (including the research coordinator with expertise in qualitative analysis) using NVivo qualitative research software. Based on the criteria of Malterud et al. [50] and previous experiences of our group, a provisional number of 50 participants (i.e., 25 PWT1D with high glucose variability and 25 PWT1D with low glucose variability) is considered a conservative initial assessment. Analyses regarding data completeness will be repeated every 3 interviews until no new relevant themes emerge (i.e., until saturation). The quantitative and qualitative data will then be juxtaposed, to deepen our understanding of appropriate and meaningful interventions and recommendations for individuals with T1D.

#### Recruitment procedures

Participants will be recruited through the endocrinology clinics in Québec City and Montreal, Canada and through the BETTER registry [33]. The multidisciplinary of the researchers and the participation of patients’ partners will contribute to the feasibility. The involvement of specialists in psychology, neuroscience, eating behaviors and nutrition, as well as of endocrinologist experts in T1D makes this project unique and ensures that all the fields covered by this study are accurately assessed. The synergy of the research professionals involved in the study will strengthen the process.

#### Feasibility

As illustrated in a recent publication by Pyatak et al. [51], remote data collection for psychological testing and CGMS can be successfully implemented by mailing study material, conducting study visits via videoconferencing, and using progressive financial compensation. At the inclusion visit, CGMS records and dietary tracking will be compensated by a $30 stipend, each session by a supplemental $15 and at the end of the procedure, a supplemental $10 stipend will be considered for full completion (i.e. < 10% of missing data). These may seem rather high, but the psychological sampling in this study is demanding and therefore such amount is more likely to ensure the feasibility of the procedure. However, it is important to also provide for the possibility of conducting the evaluation in presential session to ensure that people who do not have access to sufficient technology are not excluded from the study, therefore participants will have the option of completing the sessions at the hospital.

#### Data management

Data will be recorded and stored electronically in REDCap, hosted at the Centre Hospitalier Universitaire de Québec – Laval University. Data will be routinely checked for missing and/or erroneous values. A quality check of recorded data will be provided before the end of participants’ participation. InquisitWeb® will host cognitive tasks and will be linked to REDCap using an anonymous identifier. Data from Keenoa® app will be merged with data recording in REDCap using another anonymous identifier. At the end of the study, the principal investigator will retain an electronic copy of the cleaned data set, with all identifying information removed.

### Statistical analysis

The sociodemographic characteristics and health outcomes of individuals in the study sample will be summarized with descriptive statistics. Groups will be compared across CV statuses by using the χ2 test for categorical variables and the unpaired *t*-test for continuous variables, or nonparametric equivalent, as appropriate. ANCOVA and generalized linear models will be used to consider potential confounding factors (i.e., sex, BMI, diabetes duration, age of onset, presence of macro- or microvascular complications). Moderation-Mediation analysis will be conducted (PROCESS Macro; Fig. 2). Data curation and preprocessing will be an important part of the statistical plan. To ensure their comparability and interpretability, data will be standardized, or scaling featured, using Scikit-Learn 0.24.2 (a python library). Then artificial intelligence approaches (i.e., LASSO regression or neuronal networks) will be used to explore the potential best predictors of DEB and self-management skills.

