Insulin restriction or omission to control weight is a well-known and frequent phenomenon, affecting up to 40% of PWT1D [12, 13]. Such behavior can culminate in a particular form of disease close to anorexia nervosa called diabulimia [13]. This disorder results in dramatic increases in hemoglobin A1c (HbA1c) levels [13]. Purging or binge eating behaviors are also frequent disordered eating behaviors (DEB) in PWT1D (associated or not with restrictive eating behaviors) [14]. Moreover, the presence of binge eating behavior seems to be associated with higher anxiety and depression levels [15]. It has been demonstrated, and even mathematically modeled, that appetite is partly controlled by glycemic levels (e.g., hypoglycemia as a hunger trigger and hyperglycemia as a hunger suppressor) [16]. However, these findings are mainly based on animal studies and the impact of glycemic variability on eating behavior, and vice versa, needs to be further studied in PWT1D. Recently, Zhou et al. found that total daily energy intake does not seem to impact the glycemic variability index in PWT1D [17]. As glycemic variability is a dynamic phenomenon over the day and between days, its impact on food behavior is not likely to be detected by a change in the total amount of food consumed. More accurate reporting of both eating behavior (including loss of control eating and binge eating behaviors) and macronutrient intake (especially carbohydrate intake) may be more relevant to evaluate the consequences of glycemic variability. Moreover, we did show that inaccurate carbohydrate counting is frequent and associated with higher daily blood glucose variability in PWT1D [18]. Thus, diabetes-related numeracy will be considered a potential confounder in our study. Treasure et al. made the assumption that DEB may result in larger glycemic fluctuations [19]. Higher glycemic fluctuations may in turn affect cognitive function, potentially leading to more difficulties to maintain adequate blood glucose levels and eating behavior, thus setting up a vicious circle. Indeed, cognitive functions are highly involved in eating behavior, as they allow the modulation of food intake [20]. We recently published a meta-analysis in which we established that binge eating disorder is significantly associated with impairments in cognitive flexibility, inhibitory control, attention, and planning [21]. Thus, some of the cognitive impairments identified in PWT1D are the same as those identified in binge eating disorder. This overlap may account for DEB occurrence in PWT1D. However, there is currently limited or no evidence of the association between cognitive impairment, DEB and glycemic variability in PWT1D. The relationship between glycemic variability and DEB is challenging to establish since it could be mediated by impairment in executive functions (especially inhibitory control) and/or in interoceptive awareness (i.e., the ability to perceive body signals). Considering such parameters as potential mediators of this relationship might provide the opportunity to address this challenge.

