
Current evidence also suggests that cognitive impairment may affect treatment adherence and diabetes self-management in PWT1D [22, 23], with the potential to worsen glycemic levels. Poorly controlled diabetes may in turn worsen further cognitive functions [23, 24]. Using questionnaires, but not cognitive tasks, Vloemans et al. found that poorer executive functions are associated with higher HbA1c over time in youth with T1D [25]. The underlying mechanisms responsible for cognitive impairment in PWT1D are difficult to characterize, partly due to numerous confounding factors (e.g., age, HbA1c level, psychiatric comorbidities). Chronic hyperglycemia, longer diabetes duration, and the presence of micro- and macrovascular complications have all been associated with a higher risk of cognitive impairment in PWT1D [3]. Severe and/or repeated hypoglycemia episodes might also be involved in the increased risk of dementia in PWT1D [26]. While most studies focused on acute hypoglycemia, few have assessed glycemic variability, which better considers the broad spectrum of hyper/hypoglycemia frequency, intensity and duration. Another key limitation in current literature is the lack of reporting either hypoglycemia or hyperglycemia episodes during testing, even though it can have a direct effect on performance [24]. These limitations will be addressed in the present study. Based on the SEARCH cohort, Nip et al. were the first to explore the association between insulin sensitivity (insulin sensitivity score estimated from clinical measures including waist circumference, HbA1c, and triglyceride levels) and DEB. In PWT1D, they found that the presence of DEB was associated with greater insulin resistance and a higher body mass index (BMI) [27]. In patients with obesity, we have shown that higher dysfunctional adipose tissue is associated with greater insulin resistance and a higher severity of binge eating behaviors [28]. Hence, accounting for insulin resistance as a potential mediator of the association between glycemic variability and DEB (e.g., binge eating behavior) or cognitive dysfunction could unravel the importance of insulin resistance, even in T1D. This is especially critical since “Double Diabetes” (i.e., PWT1D displaying insulin resistance) prevalence is estimated at 30–50% of PWT1D and keeps on rising [29–31]. These data highlight the significance of this trend and the need to take into account insulin resistance as a potential mediator.

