**Fig. 2 Fig2:**
[figure not shown]
Potential mediation analysis schema with cognitive impairment, interoception and insulin resistance as potential mediators of the relationship between glycemic variability and disordered eating behaviors, using sex/gender and diabetes numeracy as moderators

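### The ANCOVA/GLM covariate list leaves out diabetes numeracy and psychotropic drug use, which the protocol elsewhere undertakes to treat as confounders, and is silent on HbA1c and psychiatric comorbidity

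*Protocol article*

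**What the plan says.** The Statistical analysis section of the protocol article compares the CV groups by χ² and t-tests or nonparametric equivalents. It then uses ANCOVA and generalized linear models to account for "potential confounding factors (i.e., sex, BMI, diabetes duration, age of onset, presence of macro- or microvascular complications". The list opens with *i.e.*, which defines a set rather than giving examples.

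Other parts of the article name further confounders:

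- Background, on carbohydrate counting: "diabetes-related numeracy will be considered a potential confounder in our study".
- Inclusion visit, on current medications: "included use of psychotropic drugs to be considered as a potential confounding factor".
- Background, on why mechanisms of cognitive impairment are hard to characterise: "partly due to numerous confounding factors (e.g., age, HbA1c level, psychiatric comorbidities".

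Numeracy reappears in the Fig. 2 legend, which describes the mediation model as "using sex/gender and diabetes numeracy as moderators". The Inclusion visit section collects the Diabetes Numeracy Test, current medications, PHQ-9, GAD-7 and "last available HbA1c (max 6 months".

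**The concern.** The primary objective compares people above and below a CV of 36%. Nobody is randomised to a CV group, so covariate adjustment is the main protection against confounding. An adjustment set that omits factors the authors say they will handle as confounders does not deliver what the rest of the article promises.

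The article itself gives reasons to take these factors seriously. It reports that inaccurate carbohydrate counting goes with higher glucose variability, which ties numeracy to the exposure. It says binge eating appears to go with more anxiety and depression, which ties mood to an outcome. It also reports that chronic hyperglycemia has been associated with cognitive impairment.

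If such a factor differs between the CV groups and also affects the outcome, a group difference can appear with no effect of variability, or a real one can be distorted. If the covariates are settled only after results are seen, the choice itself becomes a source of bias.

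**Working it through.** **Step 1. The named factors against the list.**

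| Factor | How the article describes it | Collected at inclusion | In the ANCOVA/GLM list |
|---|---|---|---|
| Diabetes numeracy | Commitment for this study (Background) | Yes, Diabetes Numeracy Test | No |
| Psychotropic drugs | Commitment for this study (Inclusion visit) | Yes, current medications | No |
| HbA1c | Confounder in the literature (Background) | Yes | No |
| Psychiatric comorbidity | Confounder in the literature (Background) | Yes, PHQ-9 and GAD-7 as screens | No |
| Age | Confounder in the literature (Background) | Yes, through onset and duration | Covered: age = age of onset + duration |
| Education | Collected only; never called a confounder | Yes | No |
| Severe hypoglycemia | Possible link to dementia; never called a confounder | Yes | No |

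The first two rows contradict the list. The next two are gaps against the article's own account of the literature. The last three rows are not contradictions.

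**Step 2. The plan's sample size, to fix the number available for adjustment.** The Sample size section gives d = -0.54, SD = 1.07, α = 0.05 and a 20% increase. It states neither power nor sidedness; I assume 80% and two-sided.

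n per group = 2 × (1.96 + 0.842)² × (1.07/0.54)² = 61.6, rounded up to 62. Then 62 × 1.2 = 74.4, rounded up to 75 per group, 150 in total. The stated figure is reproduced. (Taking 0.54 as already standardised, with 85% power, also gives 150.) If 20% of 75 are lost, 60 per group remain, 120 in all.

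**Step 3. What an omitted confounder could do.** The article gives no correlations, so every input here is an assumption.

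*Calculation A.* Let r₁ be the correlation of the factor with CV group and r₂ its correlation with the outcome, with no true effect of CV. Then spurious r = r₁ × r₂ and d = 2r/√(1 − r²). The rejection rate is that of a two-sided t-test at 60 per group.

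| r₁ | r₂ | Spurious r | Spurious d | Rejection rate (nominal 5%) |
|---|---|---|---|---|
| 0.1 | 0.3 | 0.03 | 0.06 | 6.2% |
| 0.2 | 0.3 | 0.06 | 0.12 | 10% |
| 0.2 | 0.5 | 0.10 | 0.20 | 19.4% |
| 0.3 | 0.5 | 0.15 | 0.30 | 37.8% |

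*Calculation B.* Let the factor differ by k SD between groups and have a standardised outcome slope s. Bias = k × s, with standard error √(2/60) = 0.183 and a normal approximation.

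| k | s | Bias (SD) | Share of 0.54 | Rejection rate |
|---|---|---|---|---|
| 0.2 | 0.2 | 0.04 | 7% | 5.6% |
| 0.3 | 0.3 | 0.09 | 17% | 7.8% |
| 0.5 | 0.4 | 0.20 | 37% | 19.5% |

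Both treat the factor as a pure confounder whose influence is not already captured by the five listed covariates.

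**Step 4. Can the sample carry more covariates?** Residual df = 120 − 2 − p, at one df per covariate.

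- Five listed: 113.
- Plus numeracy and psychotropic use: 111.
- Plus HbA1c, PHQ-9 and GAD-7: 108.

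**The case against.** The article condenses a fuller protocol, and reading the list as closed rests on one *i.e.* Since other sections name further confounders, the list may simply be incomplete. That explains how the mismatch could have arisen but does not remove it: what is printed as the adjustment set disagrees with what is printed elsewhere, and a reader cannot tell which governs.

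Numeracy can be both confounder and moderator, and a moderator normally enters its model with a main effect. So numeracy is conditioned on in the Fig. 2 model. This stands, and it confines the gap to the ANCOVA/GLM models. It does not close it, because the mediation model does not adjust the primary group comparison.

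The Background sentence on HbA1c and psychiatric comorbidity describes the literature and does not bind this study. This also stands. In addition, HbA1c is a component of eGDR, the insulin-resistance marker, and insulin resistance is a proposed mediator. Depression or anxiety may follow from variability. CV is already SD divided by mean glucose, so adding mean glucose changes what is estimated. These are good reasons not to make these factors compulsory covariates; they are not reasons to leave their role unstated.

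The magnitude is illustrative. Calculation A is an unadjusted comparison, and any confounding shared with sex, BMI, duration, onset or complications would already be removed. This stands.

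A reader might go further and infer that the adjusted comparison is in fact confounded. The documents do not support that, since they report no association between CV group and any omitted factor in this population. Nor do they support saying that the protocol names education or severe hypoglycemia as confounders, or that it promises an effect of variability independent of HbA1c: its hypotheses concern associations of variability with disordered eating and cognition.

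**Conclusion.** The concern holds as an internal inconsistency. The list contradicts two explicit commitments (numeracy, psychotropic drugs) and says nothing about two factors that the Background presents as confounders (HbA1c, psychiatric comorbidity). The supportable conclusion is that the adjusted comparison is left open to confounding by factors the protocol names and already measures.

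The size is unknown. Under the assumed inputs the false-positive rate at 60 per group runs from about 6%, which is negligible, to 38%, which is serious; the second set of assumptions gives about 6% to 20%. These ranges rest on assumed correlations, 20% loss and a pure confounder not captured by the listed covariates. They show that the omission could matter, not that it does. The sample size is not affected.

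**What to change.** Before analysis, amend the Statistical analysis section as follows:

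1. Keep all five listed covariates. The Background links BMI to disordered eating and vascular complications to cognitive impairment, so neither should be dropped without a reason.
2. Add the Diabetes Numeracy Test score and psychotropic drug use (yes/no) to the main ANCOVA/GLM models.
3. State that numeracy is a covariate in those models and also a moderator in the Fig. 2 model.
4. Pre-specify sensitivity models, shown with and without the added terms: one adding HbA1c (or CGM mean glucose), one adding PHQ-9 and GAD-7. Note that HbA1c enters eGDR, that mean glucose is the denominator of CV, and that mood may lie on the pathway.
5. Treat education and severe hypoglycemia as optional additions, justified on their own merits.

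No new data are needed. The main model loses two degrees of freedom (113 to 111 with 120 evaluable), and a model with all the named factors would leave 108. The remaining cost is a few additional models to run and report.
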